## Trial design {8}

The trial is a two-arm crossover multicenter randomized controlled trial conducted in France with 76 speech-language therapists as associate investigators. Randomization will be ensured by means of block randomization with a 1/1 allocation. The framework of this trial corresponds to its overall objective which is to test the superiority of a multimodal and intensive training compared with a non-specific and non-intensive training. Indeed, all children who come to seek dyslexia therapy with a speech and language therapist deserve to be helped and it is ethically difficult to justify that we postpone a potentially effective intervention for 16 months (i.e., children would lose more than an entire year, which is a lot during such a critical developmental phase). For these ethical reasons, we have decided to not to include a no-training control group.

The experiment will take place in three phases over 16 months (see Fig. 2):Phase 1 (baseline): All dyslexic readers participate in one 30-minute session per week with the speech-language therapist for 8 weeks without intensive home training. Reading and spelling exercises are performed as part of the speech and language therapy.Phase 2 (intervention): All dyslexics receive three types of intensive interventions, phonological (PHO), visual-attentional (VA), and cross-modal (CM), that last 2 month each. The order of the first two interventions (PHO and VA) is swapped in two randomly assigned groups of 60 dyslexics each. All children also participate in one 30-minute session per week with the speech-language therapist. For 15 minutes, the speech-language therapist checks that the at-home training instructions are clearly understood. The rest of the session is focused on reading and spelling exercises.

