#### Secondary evaluation criteria

Related to the secondary objectives:Reading efficiency after the phonology training and after visual-attentional training will be measured by the five reading tests in Test 3 for the two groups (G1: PHO/VA/CM, G2: VA/PHO/CM).Reading efficiency after the two phonological and visual-attentional training periods conducted in a different chronological order in each group, will be measured by the five reading tests in T4 for the two groups.Spelling skills will be measured by Chronosdictées© [120] which proposes two versions with sentences matched in length, lexical frequency and phonetic complexity.Reading comprehension will be measured by the closure test ORLEC L3© [121, 122].Reading disorder impact (reading interest, academic performance and self-esteem) will be measured by two questionnaires completed by each child and his or her parents, in which they express their degree of agreement or disagreement.

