## Statistical methods

### Statistical methods for primary and secondary outcomes {20a}

The statistical analysis will first include a descriptive analysis of the study population and the parameters studied, globally and by training group, with an assessment of absolute and relative frequencies (and their 95% confidence intervals) for categorical variables, and an assessment of means and standard deviations, medians and interquartiles for quantitative variables. A flowchart will present the number of eligible participants, the number of participants randomized into each group and the number of participants included in the final analysis. The characteristics of participants lost to follow-up during the study will be described. As recommended in the Consort recommendations, participant characteristics will be compared between the two groups at inclusion from a clinical and statistical perspective. Before each analysis is carried out, the conditions of application of the tests used will be verified. The different tests will be considered significant at the 5% threshold (first species risk).

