### Statistical analysis

To assess the gains for each dependent variable (reading, spelling and reading comprehension scores) in each group (1 and 2) and for the total sample, we will calculate the means difference and confidence intervals between T1 and T2 (Phase 1 without training), between T2 and T4 (Phase 2 after 16 weeks of training), between T4 and T5 (Phase 2 after 24 weeks of training), and between T5 and T6 (Phase 3 after 8 weeks without training).The gains between T1 and T2 will be compared with the gains between T2 and T4, between T4 and T5, and between T5 and T6 to determine whether the T2T4, T4T5, and T5T6 differences represent a significantly greater gain compared to the no training phase (T1T2).

To measure the effect of each type of training, we will calculate the effect size, *Cohen’s d* or *η*^*2*^, from the gains of each dependent variable. Cohen’s d scores of 0.3, 0.5 and 0.8 are considered to represent small, medium and large effect sizes, respectively.3.To determine whether the order of PHO/VA versus VA/PHO training leads to different effects, we will perform a repeated Anova with cross-over between groups to compare the gains between T2 and T4 of each group, controlling for gains between T2 and T1 without training. This analysis will also allow us to determine if there is a significant difference between the effects of 8 weeks of phonological training and 8 weeks of visual-attentional training between T2 and T3.4.Exploratory factor analysis will verify that all the items in the questionnaires (pre-test and post-test Likert scale) or, failing that, some of them can be combined into a score. If necessary, the composite scores will be analyzed as continuous variables. If not, graphical representations in the form of histograms will be used to visualize the variations, and χ^**2**^ tests will be carried out.

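### The order comparison controls for the Phase 1 gain without saying how; no reading biases it, but one reading wastes much of its precision, and adjusting for the T1 and T2 scores would avoid this at no cost

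*Protocol article*

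**What the plan says.** Trial design {8} defines the randomised element: "The order of the first two interventions (PHO and VA) is swapped in two randomly assigned groups of 60 dyslexics each", by "block randomization with a 1/1 allocation". Phase 1 is common to both groups: "All dyslexic readers participate in one 30-minute session per week with the speech-language therapist for 8 weeks without intensive home training". Secondary evaluation criteria states that reading efficiency after both trainings "will be measured by the five reading tests in T4 for the two groups".

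The third item of Statistical analysis gives the method. For the order question, "we will perform a repeated Anova with cross-over between groups" is the named model, and its purpose is to "compare the gains between T2 and T4 of each group, controlling for gains between T2 and T1 without training". The same analysis is to supply the comparison of phonological (PHO) with visual-attentional (VA) training between T2 and T3.

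The text does not say what role the T1–T2 gain has in the model. It gives no correlation between visits, and no effect size or power for the order question. The significance level is 5%, with sidedness not stated.

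**The concern.** Order, and PHO against VA at T3, are the only randomised comparisons in the trial. The T1–T2 gain arises before the groups are treated differently, so randomisation already makes it equal in expectation. Controlling for it can only change precision, and the direction depends on how it is done.

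Two analyses fit the sentence. A covariate model regresses the T2–T4 gain on group and the T1–T2 gain. A repeated-measures model takes the two gains as levels of a within-child factor and tests group by interval, which amounts to subtracting one gain from the other. Measurement error at T2 then enters with weight two. The two analyses can differ greatly in power, and the wording leaves the choice open until the data are in hand.

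This matters for interpretation because Secondary hypotheses (Hypothesis 5) expects no significant PHO–VA difference at test 3. An imprecise test would tend to agree with that expectation whatever the truth.

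**Working it through.** **The plan's own figure.** There is none for the order test. The sample size of 55 per group at d = 0.700 concerns baseline against intensive training. It reproduces with a two-sided 5% t-test at 95% power; the power is inferred, since the text does not state it. It says nothing about order.

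**Inputs.** From the documents: 60 per group, 10% drop-out (60 × 0.9 = 54 analysed), T1–T2 of 8 weeks, T2–T4 of 16 weeks, 5% level. Assumed: two-sided tests, unit score variance, and either equal correlation r between visits or AR(1) decay with 8-week correlation ρ (T1–T2 ρ, T2–T4 ρ², T1–T4 ρ³).

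**Step 1: same target.** Let δ be the group difference at T4. The expected group differences at T1 and T2 are 0. Hence T4 − T2 has expected group difference δ, and T4 − 2·T2 + T1 has δ − 0 + 0 = δ. A simulation with r = 0.8, 55 per group and δ = 0.40 gave a mean of 0.40 (to two decimals) for T4 adjusted for T2, for the difference of gains and for the gain as covariate.

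**Step 2: variance per child, equal correlation.**
- Plain T2–T4 gain: 2(1 − r)
- Difference of gains: 6 − 4r − 4r + 2r = 6(1 − r)
- T2–T4 gain with T1–T2 gain as covariate: 2(1 − r) − (1 − r)²/[2(1 − r)] = 1.5(1 − r)
- T4 on T1 and T2: 1 − 2r²/(1 + r) = (1 − r)(1 + 2r)/(1 + r)

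At r = 0.8 these are 0.400, 1.200, 0.300 and 0.289. The ratios to the last are 1.38, 4.15 and 1.04.

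**Step 3: variance per child, AR(1).** The difference of gains has 6 − 4ρ − 4ρ² + 2ρ³, and T4 on T1 and T2 has 1 − ρ⁴. At ρ = 0.8 these are 1.264 and 0.590, a ratio of 2.14.

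**Variance ratio to the model of T4 on T1 and T2** (equal to the ratio of required sample sizes):

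| Correlation | Plain gain | Phase 1 gain as repeated level | Phase 1 gain as covariate |
|---|---|---|---|
| Equal, 0.30 | 1.62 | 4.88 | 1.22 |
| Equal, 0.50 | 1.50 | 4.50 | 1.12 |
| Equal, 0.70 | 1.42 | 4.25 | 1.06 |
| Equal, 0.80 | 1.38 | 4.15 | 1.04 |
| Equal, 0.90 | 1.36 | 4.07 | 1.02 |
| AR(1), 0.70 | 1.34 | 2.53 | 1.29 |
| AR(1), 0.80 | 1.22 | 2.14 | 1.20 |
| AR(1), 0.90 | 1.10 | 1.80 | 1.10 |
| AR(1), 0.95 | 1.05 | 1.64 | 1.05 |

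**Step 4: illustrative power.** With 54 per group and an assumed order effect of 0.30 SD, power for the repeated-level contrast against T4 on T1 and T2, under equal correlation, is 30% v 82% (r = 0.80), 36% v 90% (r = 0.85) and 52% v 98% (r = 0.90) by simulation. A noncentral t calculation agrees within a point. Under AR(1) with ρ = 0.8 it is 28% v 52%. The covariate version loses about 0 to 2 points under equal correlation.

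**Step 5: why the proposed model is safe.** Write the analysis as T4 on group, with coefficient a on T1 and b on T2. The plain gain fixes a = 0, b = 1. The difference of gains fixes a = −1, b = 2. The gain as covariate forces a + b = 1. Each is a constrained case, so leaving a and b free cannot be less precise, apart from one or two degrees of freedom.

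**The case against.** The strongest reply is that the covariate reading is at least as natural. The sentence makes the T2–T4 gain the outcome and the groups the contrast, and controlling for a quantity is ordinary covariate language. The repeated factor could be the two cross-over periods, T2–T3 and T3–T4. On that reading little is lost, and under equal correlation above 0.5 the planned analysis is even more precise than adjustment for T2 alone. This stands: the large loss cannot be presented as what the protocol does.

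The size of the loss also depends on assumptions. The fourfold figure needs the repeated-level reading, equal correlation and a comparator that uses both T1 and T2. Against T2 alone, the ratio is 3.2 to 3.5 for r = 0.70–0.90.

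Nor is subtracting the Phase 1 gain always worse than ignoring it. If children differ in steady growth (variance s² per 8 weeks, error variance e²), the plain gain has variance 4s² + 2e² and the difference of gains s² + 6e². The latter is smaller when 3s² > 4e². This stands too, but by Step 5 the model with free coefficients on T1 and T2 is no worse in that case either.

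Finally, this is a secondary analysis in a condensed article, and a fuller document may name the model terms. But the article does state a method for its randomised contrast, and the method as stated admits two quite different tests.

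**Conclusion.** The point holds as one of ambiguity and precision. The Phase 1 control removes no bias. It costs about a factor of 4 in variance (equal correlation) or 1.6 to 2.5 (AR(1)) if the gain is a repeated level. If it is a covariate, it costs about 2–6% (equal correlation 0.70–0.90; 12–22% at 0.50–0.30) or about 5–29% (AR(1)). The correlations, the two-sided level and the 0.30 SD effect are assumptions.

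Three stronger conclusions that a reader might infer are not supported:
- That the test addresses a change in slope in place of the randomised difference at T4. T1 and T2 precede any difference in care, so the expected value is the same.
- That the order test as planned needs four times the children. The text does not commit to the reading that would require this.
- That a real order effect would usually be missed. The document gives no effect size for order, and even on the costly reading power is 52% at 0.30 SD and r = 0.90.

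This is a free improvement to a secondary analysis, not an error that invalidates it.

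**What to change.** Replace the third item of Statistical analysis with wording such as: the order effect is the difference between groups in the T4 score, estimated from a linear (mixed) model with group as factor and the T1 and T2 scores as covariates; the PHO–VA effect comes from the same model for the T3 score. Keep the therapist level foreseen in Recruitment {15}. Use the T1–T2 gain only for the within-child comparison with baseline, and neither subtract it nor make it a repeated level in the randomised comparisons.

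The cost is the rewording of one item. T1 and T2 scores are already collected, so there are no added visits, tests or children.

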### Secondary hypotheses

*Hypothesis 1*: Intensive phonological or visual-attentional training is more effective than conventional non-intensive and non-specific therapy*Hypothesis 2*: Intensive, specific, multimodal training (test 5) significantly improves reading interest, academic performance, and self-esteem compared to conventional non-intensive therapy (test 2).*Hypothesis 4*: These intervention benefits should last 2 months later (test 6).*Hypothesis 5*: No significant difference as for the effects on reading skills is expected between phonological versus visual-attentional training (test 3).

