#### Assessment of reading disability impact

Changes in reading disability, reading motivation, academic performance and self-esteem are measured by two questionnaires. These questionnaires consist of several statements for which the respondent expresses his or her degree of agreement or disagreement. Two Likert scales are constructed, one for the child, one for the parents, and are proposed before and after training (for more details, see Additional file 8).

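### The chi-square fallback for the Likert questionnaires does not fit paired, ordered answers; it is conservative and loses power for small changes

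*Protocol article*

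**What the plan says.** Item 4 of the section Statistical analysis sets a two-step plan for the questionnaires. First: "Exploratory factor analysis will verify that all the items in the questionnaires (pre-test and post-test Likert scale") can be combined into a score, using all of the items or only some. If a composite results, it is analysed as a continuous variable. The fallback reads: "If not, graphical representations in the form of histograms will be used to visualize the variations", and the same sentence then adds chi-square tests. The text does not say which table the chi-square tests use, and it names neither a paired nor an ordinal form.

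Three other places fix the kind of data and the question:

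- Assessment of reading disability impact: "Two Likert scales are constructed, one for the child, one for the parents, and are proposed before and after training". For each statement, "the respondent expresses his or her degree of agreement or disagreement". The number of answer levels is not given in the article, which refers to an additional file.
- Secondary hypotheses, Hypothesis 2: "Intensive, specific, multimodal training (test 5) significantly improves reading interest, academic performance, and self-esteem compared to conventional non-intensive therapy (test 2").
- Trial design: every child receives all three trainings, so there is no untrained group to compare with.

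**The concern.** The data are repeated ordered answers from the same respondents, and the hypothesis concerns change within the child. An ordinary Pearson chi-square on a table of time (before, after) by answer level treats the two sets of answers as coming from different people. It also treats the levels as unordered categories, so a steady move from disagreement towards agreement counts for no more than a haphazard reshuffling.

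Reading interest, academic performance and self-esteem are a stated secondary objective with their own hypothesis. If the fallback is used, a small but real improvement could be missed because of the test rather than the data.

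**Working it through.** **No figure to reproduce.** The article gives no power, sample size or separate alpha for the questionnaires. The check is a simulation of how the named test behaves on this kind of data.

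**Inputs from the article**
- 120 children included, 10% drop-out expected (Sample size {14}): 120 × 0.90 = 108 completers.
- Significance threshold 5% (Statistical methods {20a}); taken as two-sided.
- Same respondents before and after, ordered agreement scale (Assessment of reading disability impact).
- Effect-size labels: d = 0.3 small, 0.5 medium (Statistical analysis).

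**Assumptions not in the article**
- One item with five levels, equally likely before training.
- Latent normal answers cut at the quintiles, with pre/post correlation ρ from 0 to 0.8.
- Latent shift of 0, 0.3 or 0.5 SD.

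**Why the direction is predictable.** For answer level k, the variance of the pre/post difference in proportions is [p₁ₖ(1−p₁ₖ) + p₂ₖ(1−p₂ₖ) − 2cₖ]/n, where cₖ is the within-child covariance of choosing level k on both occasions. The Pearson statistic Σ(O−E)²/E on the 2 × 5 table (4 degrees of freedom) omits cₖ. With positively correlated answers it overstates the variance, so it rejects too rarely. Spreading the test over 4 degrees of freedom rather than aiming it at a shift costs further power.

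**Results, n = 108, 4,000 runs per setting.** Stuart-Maxwell is included as a paired test that still ignores order.

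| ρ | Pearson, no change | Wilcoxon, no change | Pearson, 0.3 SD | Stuart-Maxwell, 0.3 SD | Wilcoxon, 0.3 SD |
|---|---|---|---|---|---|
| 0 | 4.9% | 4.6% | 35% | 33% | 53% |
| 0.3 | 3.5% | 5.1% | 33% | 45% | 66% |
| 0.5 | 2.4% | 5.0% | 29% | 57% | 79% |
| 0.7 | 1.5% | 5.2% | 23% | 78% | 93% |

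The row ρ = 0 isolates the cost of ignoring order, because pairing plays no part there: 35% against 53%. Further down the table the Pearson test worsens and the paired tests improve. Results at n = 120 are similar (at ρ = 0.5: 31% against 81%).

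**Separate simulation, wider correlations and a larger shift (n = 108)**

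| ρ | Pearson, no change | Pearson, 0.3 SD | Wilcoxon, 0.3 SD |
|---|---|---|---|
| 0.3 | 3.3% | 33% | 66% |
| 0.6 | 1.3% | 25% | 84% |
| 0.8 | 0.9% | 20% | 98% |

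At a 0.5 SD shift over the same correlations, Pearson power is about 83–90% and Wilcoxon power about 97–100%.

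**Other tables the wording could mean**
- Pre-by-post cross-table with a Pearson test: this tests association, not change. With no change at all and ρ = 0.5 it rejects in 90% of runs.
- Group 1 against Group 2: valid as a test of independent children, but it does not address Hypothesis 2, since both groups receive all trainings.
- Counts of improved against worsened children: this uses the pairing. At ρ = 0.6 and 0.3 SD its size is 5.4% and its power 82%, against 86% for Wilcoxon.

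**The case against.** The strongest defence is that the article does not state the faulty test. It says chi-square tests and no more. That family includes McNemar, Bowker and Stuart-Maxwell, and the reference to variations could mean each child's change. If the test compared improved with worsened counts, the loss would almost vanish. The article also promises to check the conditions of each test before use. This stands in part: the Pearson reading is the natural one, not the only one. But no paired form is named, the promised check names no replacement, and Stuart-Maxwell and Bowker would still discard the order.

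A second defence is that this is a detail for an analysis plan. The article does name the test, however, so the point concerns a stated choice rather than an omission. The reach is still small: the fallback applies only if neither all nor some of the items form a score, and the reading outcomes are untouched.

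Three stronger readings are tempting and are not supported:

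- *A real change would probably be reported as none.* This holds only for small shifts. At 0.5 SD even the Pearson test detects the change in about 83–90% of trials.
- *The test would produce false claims of benefit.* On the time-by-answer reading with positively correlated answers, the error is conservative.
- *The factor analysis lets post-training answers shape the score in favour of training.* The wording, "pre-test and post-test Likert scale) or, failing that, some of them can be combined into a score", does not say that the two occasions are pooled; separate analyses fit it equally well. Factor analysis groups items by their correlations, not by whether they improved. This is not an error in the plan.

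**Conclusion.** The point holds in limited form. For ordered answers from the same children and parents, and a within-child hypothesis, an unqualified chi-square test is a poor fallback: on its natural reading it ignores the pairing, and on almost any reading it ignores the order. The price is a false-positive rate of about 1–3% in place of 5% and a marked loss of power for a small change (about 33% to 20%, against 66% to 98%, at 0.3 SD). The loss is minor for a medium change.

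These figures rest on five equally likely levels, 108 completers and correlations of 0.3 to 0.8, none of which the article gives except the inputs to the 108. The direction does not depend on the exact values as long as a respondent's answers before and after are positively correlated. Because the table is unspecified and the analysis is a conditional fallback for a secondary outcome, this is a modest correction and does not threaten the trial's main conclusion.

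**What to change.** In item 4 of Statistical analysis, replace the chi-square fallback with a paired ordinal analysis of each item, test 5 against test 2, done separately for the child and the parent scale: either the Wilcoxon signed-rank test or an ordinal mixed model with child as random effect. The histograms can stay as description. If answers are deliberately treated as nominal or dichotomised, name Stuart-Maxwell or McNemar, so that the pairing is at least respected.

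The cost is one sentence. It needs no extra data, visits or children.

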### Interim analyses {21b}

The baseline scores obtained monthly during Phase 2 will also be analyzed according to the same statistical strategy presented earlier in 20a.

### Methods for additional analyses (e.g. subgroup analyses) {20b}

Any additional subgroup analysis will depend on the sample sizes of the subgroups analyzed. However, multiple case studies will be considered if necessary.

